### EMA assessment schedule

During the 14 days of active assessments, patients receive notifications (‘beeps’) in the TIKI-App on their smartphones eight times a day at quasirandom intervals of 90±30 min. Depending on their individual sleep—wake rhythm, participants can choose to receive beeps between 7.30 and 21.30 or 09.30 and 22.30. The respective questionnaires expire after 30 min. Each EMA assessment contains 30–35 items in total, depending on assessment phase and timing. The order of items was pseudorandomised.

We employ graded reimbursement, as it was shown to increase compliance: participants received at least 20€ per assessment phase, 35€ if they completed at least 90 beeps and 50€ if they completed more than 100 beeps. Thus, participants receive up to 150€ for the EMA assessments, which are paid out as a gift voucher. Moreover, individuals participating in the long version of the study are allowed to keep the smartwatch.

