### Data preprocessing and feature engineering

In its raw format, passive sensing data are usually not interpretable. Thus, depending on the data source, data format and research question, different data preprocessing and aggregation steps will be necessary.

GPS data are collected as tuples containing coordinates (ie, Latitude and Longitude values). To clean and preprocess the data and build ML features, we follow guidelines by Müller *et al* (35). We adapt them to our event-based sampling format, where GPS was assessed when a location change was detected. From GPS data, we will calculate movement patterns in predefined timescales, that is, location entropy, distance travelled or time spent at home.Passive data derived from the Withings Scanwatch will be further preprocessed where possible and necessary, as Withings does not provide raw data for most data sources (see table 1). Here, we align our preprocessing steps with guidelines for preprocessing sensor data (36). From continuous PPG-based heart ate data, we are able to build features like average HR, min/max HR and HR-zones. From the resting-state ECG,we can create more fine-grained features like HRV. For sleep, we will calculate features describing sleep quality, that is, sleep duration, proportion of sleep phases and sleep efficiency (i.e. sleep duration/ time in bed) per night. Activity features describe the amount of, or time in active or inactive states, that is, total number of steps or time spent walking/running/cycling and the amount of calories burned.For EMA data, we will calculate the RMSSD (that is, for emotional inertia or ER variability), individual SD and mean values. Further feature engineering steps for EMA are described in the *Analysis* section.

Depending on the research question and granularity of data aggregation, a certain compliance rate has to be met to be included in the analysis (ie, at least 50% of completed EMA beeps). Missing data imputation will also depend on the type of data and applied analyses.

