#### Model development

Within the development set, we apply nested, repeated, stratified fivefold cross-validation. In each outer fold, 80 % of development data form the training subset and 20 % the validation subset for hyperparameter tuning and model selection. Performance metrics are averaged across folds and repetitions to yield optimism-corrected estimates. The optimised pipeline is then evaluated on the untouched 20 % hold-out test set.

Exploratory analyses that do not involve model building are conducted exclusively within the development set to safeguard the integrity of the hold-out sample.

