#### Predictive analyses

We will implement both basic and advanced models and compare subsets of data and different timeframes to balance interpretability and predictive performance. With a sample size of at least 350 participants, we have sufficient data to explore a range of methods.

There are various ways to aggregate and preprocess EMA data to include them as predictors of non-response, ranging from simple aggregates to advanced modelling techniques. We will implement dynamic structural equation models (DSEM), an advanced extension of multilevel modelling that integrates time-series dynamics with latent variable modelling.^30^ Multilevel models are considered the gold standard for longitudinal data analysis in psychology,^31^ and DSEM builds on this foundation to allow unequally spaced observations and modelling of time-lagged dependencies, making it well suited for EMA data. The Bayesian estimation approach allows for missing data under the missing at random assumption (eg, when participants skip measurements). Beyond that, DSEM models are extendable to model change in dynamic parameters across measurement bursts. Further, passive data can be flexibly integrated into DSEM to analyse cross-lagged relationships between EMA (ie, affect) and passive sensing features (ie, sleep and physical activity). The model-based framework allows us to derive dynamic parameters (eg, individual autocorrelations and cross-lagged relationships) that we will use as features for the predictive analyses.

For the prediction of NR, basic algorithms include logistic regression, support vector machines, random forests and gradient boosting, depending on the research question and predictors used. Tree-based approaches are known for their effectiveness on tabular data.^32^ Regression-based approaches are highly interpretable. All of the selected require fewer computational resources compared with deep learning models and were frequently applied in psychotherapy research, increasing comparability.^33^,^35^

Advanced modelling approaches will be selected to incorporate the hierarchical, sequential and multimodal structure of our data. These include deep learning architectures like LSTM, Transformers or ensemble learning approaches. To explore how the predictive capacities depend on the time lag, we compare the accuracies of models using subsets of available data (eg, first measurement burst vs second measurement burst) and outcome timepoints (ie, T20 vs TPost).

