## Discussion

Within the research endeavour of the PREACT study to find predictors of non-response to CBT for ID, PREACT-digital implements therapy accompany digital phenotyping. DP complements the other subprojects by contributing dense, behavioural and physiological information from the patients everyday life, providing an ecologically valid and innovative add-on to more traditional sources of data. By integrating EMA with wearable-based passive sensing, we capture detailed, real-time information that goes beyond traditional cross-sectional snapshots. Our predictive analyses aim to determine whether advanced but computationally demanding modelling approaches improve accuracy over simpler methods, while exploratory analyses focus on uncovering potential mechanisms and subgroups that may inform tailored interventions.

A key strength of our study lies in its ecological validity: participants provide data in naturalistic settings, resulting in rich, high-frequency observations. We further benefit from a relatively large sample size and the opportunity to capture change processes over multiple time points. The integration of our project into the Research Unit allows us to compare our digital phenotypes with other data modalities and acquire a rich, comprehensive impression of participating patients. Although a few studies have integrated DP into outpatient therapy settings, this combination of different data modalities is unique to our study.

Despite these strengths, there are also key limitations that demand consideration. First, the study includes no healthy control group. As a result, we cannot directly distinguish digital patterns that are specific to clinical presentations from those also present in non-clinical populations. Future work will need case–control or population-based designs to clarify the specificity of any digital signatures identified here. Second, the extensive assessment schedule may place a burden on participants. Although we tried to keep the length of our active assessments reasonable (ie, around 3–5 min to complete it), answering eight daily questionnaires across 14 days is non-negligible. Also, participants are asked to wear their smartwatch as continuously as possible, also during nighttime. This combination of frequent questionnaires and continuous sensing may reduce adherence over time and, in the worst case, could lead some participants to withdraw from the study.

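### EMA compliance as a condition for entering an analysis makes EMA-based accuracy conditional on adherence, with no allowance in the sample, the hold-out or the model comparison

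*Protocol article*

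**What the plan says.** The rule is in the protocol article under *Data preprocessing and feature engineering*, the section that builds the machine-learning features. "Depending on the research question and granularity of data aggregation", it says, "a certain compliance rate has to be met to be included in the analysis (ie, at least 50% of completed EMA beeps"). The next sentence leaves imputation open: "Missing data imputation will also depend on the type of data and applied analyses".

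Other sections bear on it:

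- *EMA assessment schedule*: "During the 14 days of active assessments, patients receive notifications" "eight times a day at quasirandom intervals of 90±30 min".
- *Sample size calculation*: 585 PREACT patients, of whom about 80% (468) join PREACT-digital, and 75% of those (350) choose the long version.
- *Data freeze, holdout and model training*: a participant-level hold-out of 20%, stratified by age, sex, primary diagnosis and data modality. Compliance is not a stratum.
- *Model development*: "The optimised pipeline is then evaluated on the untouched" 20% hold-out set.
- *Predictive analyses*: a sample of at least 350 is called sufficient. A model on cross-sectional intake data is compared with EMA-only, passive-only, EMA-plus-passive and all-source models by paired AUC differences with the DeLong test. On missing data, the Bayesian DSEM estimation "allows for missing data under the missing at random assumption (eg, when participants skip measurements").
- *Discussion*: "This combination of frequent questionnaires and continuous sensing may reduce adherence over time".

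**The concern.** Entry into an analysis depends on how the participant behaves during the same window that supplies the predictors. A model trained and tested only on people who pass the cut has a performance estimate for people who pass the cut. The end of the *Introduction* and the *Discussion* aim at markers that can be used in routine care to find patients at risk of non-response early, and those patients include people who answer few beeps.

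Three further things follow where the cut is applied. The hold-out that is actually scored is smaller than the one drawn. The planning figures of 468 and 350 contain no allowance for the loss. And a cut on EMA beeps need not affect the intake-only and passive-only models, so the compared models could be fitted and tested on different people, whereas a paired AUC test needs each patient scored by both models.

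The missing-at-random statement for DSEM does not repair this. It concerns beeps skipped by people who are analysed, not people whom the cut removes.

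**Working it through.** **The plan's own figures.** 585 × 0.80 = 468, as stated. 468 × 0.75 = 351, stated as 350. The 585 itself comes from simulations in the main protocol, which is not shown, and cannot be rebuilt here.

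**The example cut.** 8 × 14 = 112 beeps per burst, and 50% of 112 = 56. A participant with 55 completed beeps would fail it.

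**Hold-out before exclusion.** 0.20 × 468 = 93.6, about 94. For the long version, 0.20 × 350 = 70.

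**Effect of exclusion on size and precision.** No exclusion rate is given, so the excluded share d is an assumption, shown from 10% to 40%. Hold-out size is n = 0.20 × N × (1 − d). The 95% half-width around an accuracy of 75% is 1.96 × √(0.75 × 0.25 / n).

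| d | T0 sample | Hold-out | Half-width (points) | Long version | Hold-out | Half-width (points) |
|---|---|---|---|---|---|---|
| 0% | 468 | 94 | 8.8 | 350 | 70 | 10.1 |
| 10% | 421 | 84 | 9.2 | 315 | 63 | 10.7 |
| 20% | 374 | 75 | 9.8 | 280 | 56 | 11.3 |
| 30% | 328 | 66 | 10.5 | 245 | 49 | 12.1 |
| 40% | 281 | 56 | 11.3 | 210 | 42 | 13.1 |

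These counts take no account of missing outcomes, which would lower every row.

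**The figure of at least 350.** In the long version, any exclusion takes the number below 350. For models that use only the first burst, the base is 468, and the number stays at 350 or more until about (468 − 350) / 468 = 25% are excluded.

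**Effect on what the accuracy means.** Accuracy in all = (1 − d) × accuracy in compliers + d × accuracy in the excluded. Suppose it is exactly 75% in compliers and, as an assumption, 50–65% in the excluded:

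- d = 10%: 72.5–74.0%
- d = 20%: 70.0–73.0%
- d = 30%: 67.5–72.0%
- d = 40%: 65.0–71.0%

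If accuracy in the excluded is also 75%, nothing changes. The documents do not say which case applies.

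**The case against.** The other side has a good deal of substance.

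- **Scope.** The sentence covers analyses in general, including the exploratory ones, and does not name prediction. The article often uses *ie* to introduce examples, so 50% reads as an illustration. This stands, and it is why the point is limited to wherever the cut is applied to EMA-based models. But the rule sits in the section that builds the predictors, and no exemption is given.
- **Deferred detail.** The exact threshold and the imputation method may be in the full plan or in the code promised on OSF and GitHub. This also stands, and their absence from the article is not the point. The point is the exclusion rule that the article does state.
- **A floor has a measurement reason.** RMSSD, individual SDs and individual autocorrelations need enough beeps per person. This stands too. It is a reason to keep a complier analysis, but not to make it the only result.
- **Mitigation.** Weekly monitoring of passive and GPS data, mails on completion rates and payment tiers at 90 and above 100 beeps should limit the loss. They may make d small, but they do not change who is analysed. Opting in already selects participants, and adherence is listed as a limitation, though without a link to who is analysed.

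A reader might infer three stronger things that the documents do not support. First, that low compliers are deleted from every prediction model: an EMA cut need not touch the intake-only or passive-only models. Second, that the cut could be moved once hold-out results are known: varying by research question is not varying by result, and a threshold fits naturally into a pipeline settled during development. Third, that the rule removes non-responders disproportionately and inflates accuracy: this needs non-response rates by compliance, and the documents give none.

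**Conclusion.** The point holds in a bounded form. As written, inclusion may depend on a compliance rate that differs between questions, and the predictive models are not exempt. Where the cut is applied to EMA-based models, the result against the target of more than 75% applies to adherent participants, not to all participants starting CBT who supplied digital data.

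The arithmetic consequence is a hold-out below 94 of 468: 84 to 56 if 10–40% are excluded, with the half-width widening from 8.8 to between 9.2 and 11.3 points. That range is assumed. The size and direction of any bias in accuracy are unknown, and it could be nil. The risk that the compared models rest on different patients depends on whether the cut is applied to all of them, which the article does not say.

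**What to change.** For the predictive analyses:

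1. Set one compliance cut before the hold-out is opened.
2. Report hold-out performance for all participants with any T0 digital data and an outcome, alongside the result restricted to compliers. Compute EMA aggregates from the beeps available and use completed-beep count and watch wear time as features. Where variability or dynamic features cannot be estimated, use in-fold imputation or missing indicators.
3. Run the paired AUC comparisons on a common patient set.
4. Report the number and the outcome rate of those whom the cut removes.

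No new data are needed: completion counts already determine the payments and appear in the update mails. The cost is a change of wording and one extra run. The downside is noisier features for low compliers and possibly a slightly lower accuracy in the all-participant result.

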### Analysis

The analysis procedure and code will be provided on OSF and on Github (https://github.com/[name]/preact_digital). Data preparation, exploration and modelling will mainly be done using Python, R in the Jupyter Lab environment, conducted on the computing facility of Charité – Universitätsmedizin Berlin.

#### Data freeze, holdout and model training

To allow for exploratory analyses without risking data leakage for predictive modelling, all data collected up to November 2024 were frozen. PREACT then drew an a priori, participant-level hold-out sample comprising 20 % of the cohort, stratified by age, sex, primary diagnosis and data modality (EEG, MRI, digital-phenotyping short vs long). The remaining 80 % constitute the development data set.

Participants enrolled after November 2024 (ie, after the data freeze) are assigned to development or hold-out according to the same 80 : 20 stratified rule so that these proportions are preserved when recruitment closes in June 2025.

#### Model development

Within the development set, we apply nested, repeated, stratified fivefold cross-validation. In each outer fold, 80 % of development data form the training subset and 20 % the validation subset for hyperparameter tuning and model selection. Performance metrics are averaged across folds and repetitions to yield optimism-corrected estimates. The optimised pipeline is then evaluated on the untouched 20 % hold-out test set.

Exploratory analyses that do not involve model building are conducted exclusively within the development set to safeguard the integrity of the hold-out sample.

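### The cross-validation is called nested, but the described split tunes, selects and scores on the same outer 20%; followed literally, it overstates development-set performance

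*Protocol article*

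**What the plan says.** Three consecutive sentences under Model development set out the scheme:

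- The label: "Within the development set, we apply nested, repeated, stratified fivefold cross-validation".
- The split, and the claim made for its result: each outer fold trains on 80% of the development data, and the other 20% is "the validation subset for hyperparameter tuning and model selection. Performance metrics are averaged across folds and repetitions to yield optimism-corrected estimates".

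The section then adds a separate final step: "The optimised pipeline is then evaluated on the untouched 20 % hold-out test set". The hold-out itself is described under Data freeze, holdout and model training: "PREACT then drew an a priori, participant-level hold-out sample comprising 20 % of the cohort". The other 80% is the development set.

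Under Predictive analyses the article lists four basic algorithms, then LSTM, Transformers or ensembles. It sets a baseline cross-sectional model against four richer model sets, with separate models for T20 and TPost, and reports paired AUC differences with DeLong tests. It also says "we compare the accuracies of models using subsets of available data". It does not say whether these comparisons are made on the development folds or on the hold-out.

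**The concern.** Nested cross-validation keeps two jobs apart. Inner folds, cut from the outer-training data, choose the configuration; the outer fold only scores the choice. The article gives the choosing to the outer 20%, describes no inner split, and names no other part of the development set from which the averaged metrics could come. On its face the same patients choose the winner and mark it.

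A score obtained that way is too high on average, and the article would publish it as corrected for optimism. The Introduction notes that earlier prediction studies often did little better than chance, so a procedure that can make noise look modestly predictive matters here. The development figures also decide which pipeline goes to the hold-out, and readers may rely on them because the hold-out is small.

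**Working it through.** **1. Roles of the outer 20%.** The split sentence assigns it tuning and model selection. The next sentence averages metrics across the folds and repetitions. With no inner split described, the averaged metrics can only be those of the same outer 20%. This conflicts with the nested label and with the claim of optimism correction.

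**2. Sizes.** From Sample size calculation: 585 × 0.80 = 468 at T0, as stated; 468 × 0.75 = 351, stated as 350. Applying the 80:20 rules:

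- N = 350: development 280, hold-out 70; each outer fold 224 / 56.
- N = 468: development 374, hold-out 94; each outer fold 299 / 75.

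These are before any dropout or exclusion for low compliance.

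**3. Direction.** Let candidate k have true AUC A_k and observed AUC A_k + e_k on a given 20%, with E(e_k) = 0. Then E[max(A_k + e_k)] ≥ max A_k, and the true AUC of the chosen candidate is at most max A_k. The reported maximum is therefore biased upward. Averaging such maxima over folds and repetitions reduces variance but leaves the bias. If instead one configuration is chosen on its mean over the same folds, the errors are smaller, and so is the bias, but it remains positive.

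**4. Size, simulation A (assumed set-up).** 60 features; 20 configurations (5 feature sets × 4 ridge penalties); 50% prevalence; 100 data sets per setting. Signal is a mean shift in three features. True AUC of the selected models, in brackets, comes from 4,000 independent cases.

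| Development n | Shift | Best per outer fold | One configuration on fold mean | Properly nested |
|---|---|---|---|---|
| 280 | 0 | 0.579 (0.498) | 0.550 | 0.503 (0.499) |
| 280 | 0.3 | 0.628 (0.547) | 0.596 | 0.553 (0.549) |
| 280 | 0.5 | 0.684 (0.620) | 0.659 | 0.632 (0.629) |
| 374 | 0 | 0.573 (0.501) | 0.545 | 0.503 (0.500) |
| 374 | 0.3 | 0.618 (0.553) | 0.591 | 0.553 (0.555) |
| 374 | 0.5 | 0.689 (0.634) | 0.670 | 0.651 (0.649) |

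Per-fold selection overstates by between 0.689 − 0.634 = 0.055 and 0.579 − 0.498 = 0.081. Selection on the fold mean exceeds the nested figure by between 0.670 − 0.651 = 0.019 and 0.550 − 0.503 = 0.047. Proper nesting is within 0.004 of the truth throughout.

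**5. Size, simulation B (different assumptions).** 60 features; 28 configurations (7 feature sets × 4 penalties); about 60% non-response; fivefold × 2 repetitions; 60 data sets per setting; no signal. In the order per fold / fold mean / nested: n = 374 gives 0.588 / 0.552 / 0.508; n = 280 gives 0.603 / 0.562 / 0.512.

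**6. Sensitivity.** Best of K equally good candidates, K = 5, 20 or 50, score correlation 0.5, 0.8 or 0.9, true AUC 0.50 or 0.65, development n 280 or 374. Inflation runs from +0.024 to +0.128 for per-fold selection and from +0.010 to +0.054 for selection on the fold mean.

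**7. Precision of the hold-out.** Hanley–McNeil, assuming AUC 0.65 and 60% non-response. Q1 = 0.65/1.35 = 0.4815, Q2 = 2 × 0.65²/1.65 = 0.5121.

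- 70 patients (42/28): variance = [0.2275 + 41 × 0.0590 + 27 × 0.0896]/1176 = 0.0043; 95% half-width about 0.13.
- 94 patients (56/38): variance = [0.2275 + 55 × 0.0590 + 37 × 0.0896]/2128 = 0.0032; 95% half-width about 0.11.

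**The case against.** The strongest reply is that this is a slip of wording. The terms nested and outer fold imply an inner fold, the optimism claim fits genuine nesting, and a journal article condenses a longer plan; the Analysis section promises procedure and code on public repositories. This stands in part: one cannot conclude from the article that the analysis will be run this way. It does not remove the point. The article does not leave the allocation open; it states one, and that one is not nested. Code that followed the sentence would be biased, and code that departed from it would contradict the published protocol.

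The second reply is that the hold-out protects the result. For the final estimate this is right: a set drawn in advance and not used for tuning is free of this optimism. The development figures would still carry a label they have not earned.

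Three stronger readings are tempting, and the documents do not support them:

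- *The bias favours the advanced models over the simple ones.* Optimism grows with the number of candidates tried, whichever family they come from, and a simple model with a large grid gains too. The simulations used ridge models only and tested no flexible method.
- *The bias is as large as the increments the study hopes to detect.* No AUC increment is stated. The only target is accuracy above 75%.
- *Every algorithm, model set and outcome time adds to the selection.* T20 and TPost are separate targets with separate models, and the model sets are planned contrasts. Neither is shown to compete in one selection.

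**Conclusion.** The passage is wrong as written and needs correcting. It contradicts its own label, and a team that followed it literally would obtain development-set metrics biased upward. The direction follows from the stated rule; the size does not, because the grid size, the correlation between candidates and the non-response rate are all assumed. With 20 to 28 configurations and no signal, the reported AUC is about 0.57 to 0.60 under per-fold selection, which is the most extreme reading, and about 0.545 to 0.56 under selection on the fold mean, against about 0.50 to 0.51 with proper nesting. Over the wider set of assumptions the inflation is about 0.01 to 0.13.

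A reader might infer that the study's final performance claim is compromised. It is not, as far as that claim rests on the hold-out. But the hold-out has only about 70 to 94 patients, and because the set used for the accuracy and DeLong comparisons is not named, those comparisons may or may not inherit the bias.

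**What to change.** Replace the split sentence under Model development with a statement of three things:

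1. In each outer fold, all data-dependent preprocessing, feature derivation (including DSEM parameters and any cluster membership used as a feature), hyperparameter tuning and model selection are done by inner cross-validation within the 80% outer-training subset.
2. The outer 20% is used once, only to score the model chosen in the inner loop.
3. Only these outer scores are averaged and called optimism-corrected.

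Then state how the hold-out pipelines are fixed: rerun the same inner tuning procedure on the full development set, separately for each prespecified model set and each outcome time. Inner loops may choose different configurations in different folds, so they do not by themselves give one final pipeline. Keeping one pipeline per model set also leaves the planned model-set comparisons possible on the hold-out. Under Predictive analyses, name the data set on which the accuracy and DeLong comparisons are made.

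Cost: the text change is short. With K configurations and five inner folds, the fits per outer fold rise from K to 5K + 1, for example from 20 to 101, plus the final rerun on the development set. Running time cannot be given from the article and will be greatest where Bayesian DSEM features or deep networks are refitted in every inner fold. Development-set figures will look less favourable. If the team does not nest, the claim of optimism correction should be removed.
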